## Abstract

**Background:**

Many patients with chronic insomnia disorder (CID) have gastrointestinal (GI) symptoms. First-line insomnia medications do not treat GI problems. Acupuncture has a comprehensive regulative action on both CID and GI disorder and is receiving increasing attention. Recent studies indicate that both CID and GI diseases may cause abnormal brain activity. However, the neurological mechanism underlying the effect of acupuncture on such diseases is still unclear. The aim of this study is to explore the pathological mechanisms of CID with GI discomfort, as well as the main response characteristics of acupuncture treatment from multiple perspectives using multimodal magnetic resonance imaging (MRI).

**Methods:**

A total of 60 participants with CID and GI disorders will be randomly divided into two groups (real acupuncture group and sham acupuncture group; ratio of 1:1). Patients will receive 20 sessions (five sessions per week) of real acupuncture treatment or sham acupuncture treatment. The primary outcome is the aggregate score on the Pittsburgh Sleep Quality Index. Secondary outcomes are scores on the Gastrointestinal Symptom Rating Scale, Self-Rating Anxiety Scale, and Self-Rating Depression Scale. Multimodal MRI scans and clinical assessments will be performed both at baseline and post-treatment. Another 30 age-, sex-, and education-matched healthy subjects will be recruited as controls and will receive MRI scans and clinical evaluations.

**Discussion:**

This study aims to provide scientific evidence for the mechanism of acupuncture in treating CID with GI disorder using multimodal MRI imaging data on brain structure, function, and metabolism.

**Trial registration:**

Chinese Clinical Trial Registry, ChiCTR1800017092 (URL: http://www.chictr.org.cn/showproj.aspx?proj=27173). Registered on July 11, 2018.

**Supplementary Information:**

The online version contains supplementary material available at 10.1186/s13063-021-05332-3.

## Background

Chronic insomnia disorder (CID) is defined as difficulty initiating or maintaining sleep that is associated with daytime consequences and occurs at least three times per week for more than 3 months; CID has a prevalence rate of 5% to 10% [1]. Typical nighttime symptoms include difficulty falling asleep, difficulty maintaining sleep, and waking early [2, 3]. Additional symptoms include fatigue, memory decline, cognitive deficits, and mood disorder [4, 5]. Recent studies have identified a correlation between sleep disturbances and gastrointestinal (GI) diseases [6]. According to a previous survey [2], about 27.5%–33.4% of insomnia patients have concomitant GI symptoms, such as dyspepsia, diarrhea, and constipation. Interestingly, patients with multiple GI symptoms are more likely to have sleep problems [7–9]. It has recently been suggested that GI function plays a vital role in sleep [10]. These findings provide new insights into the pathological features and treatment of CID associated with GI.

Pharmacotherapy is the primary recommended treatment for CID, according to the American Academy of Sleep Medicine clinical practice guideline [1]. Although there is evidence for the short-term efficacy of insomnia medications [11, 12], long-term use is associated with the risk of addiction and adverse drug reactions, particularly GI side effects [13]. Therefore, treatments with fewer side effects are needed for this population. Acupuncture is a possible alternative therapy. Multiple studies have shown that acupuncture effectively improves sleep quality [14, 15]. Other studies have found that acupuncture can improve inflammation in gastrointestinal diseases and promote the recovery of gastrointestinal function [16–18]. Moreover, acupuncture is more effective than drug therapy in treating insomnia with GI disorder [19, 20]. However, the mechanism underlying the effect of acupuncture on CID with GI symptoms remains to be elucidated.

In recent years, magnetic resonance imaging (MRI) techniques, such as functional magnetic resonance imaging (fMRI), structural magnetic resonance imaging (sMRI), diffusion tensor imaging (DTI), and magnetic resonance spectroscopy (MRS), have been widely used to study the pathophysiological mechanisms of insomnia. Using fMRI, we previously confirmed that the core pathological features of patients with CID are evident in the structural and functional plasticity of the brain [21–24]. DTI technique is currently the only non-invasive method to effectively observe and track white matter fiber tracts. One study found that compared with healthy people, the fractional anisotropy (FA) value of the anterior internal capsule in insomniacs decreased [25]. Another study also found that the diffusion properties of the right arcuate fasciculus and the superior longitudinal fasciculus, such as the values of FA, mean diffusivity (MD), radial diffusivity (RD), and axial diffusivity (AD), were changed in insomnia patients [26]. By analyzing the diffusion properties of white matter, we can infer the influence mechanism of acupuncture on the white matter of CID patients with GI disorder. MRS is the only non-invasive method that can quantify biochemical substances in the brain [27], and MRS studies have identified abnormal brain metabolic activity in insomnia patients [28, 29]. Such studies have helped to clarify the pathology and treatment mechanisms of CID with GI disorder.

There is growing evidence from MRI studies that acupuncture can restore abnormal brain structure, connections, and metabolism in pathological states [30–32]. Both insomnia [33] and GI disease [34] studies have shown that acupuncture can repair abnormal connections in the brain. Previous studies on the mechanism of acupuncture in treating CID have shown that acupuncture affects the activation of brain regions through tactile somatosensory specific stimuli [35, 36]. Acupuncture can regulate the activity of specific brain regions related to sleep experience, such as the prefrontal lobe, temporal lobe, parietal lobule, anterior cingulate, supramarginal gyrus, and precuneus [36–38]. In addition, acupuncture can also regulate cerebral blood flow and neurotransmitter levels such as 5-hydroxytryptamine (5-HT), gamma aminobutyric acid/glutamate (GABA/Glu) in the brain of patients with insomnia [39, 40]. At present, neuroimaging technology has become the mainstream means to study the mechanism of acupuncture treatment of CID. However, no studies have focused on the mechanism underlying the effect of acupuncture on CID with GI disorder. Therefore, a multimodal MRI approach combining fMRI, sMRI, DTI, and MRS is needed to explore the main mechanisms by which acupuncture affects CID with GI disorders.

For these reasons, we designed this multimodal neuroimaging trial. The study aims are as follows: (1) to confirm the efficacy of acupuncture for patients with insomnia and GI discomfort by comparing it with sham acupuncture; (2) to explore the central response mechanism underlying the effect of acupuncture on CID with GI disorders, focusing on cerebral structure, function, and metabolism; (3) to explore a possible correlation between brain activity changes and symptom improvement caused by different acupuncture modes.

## Methods/design

The protocol was developed in accordance with Standard Protocol Items for Clinical Trials with Traditional Chinese Medicine 2018 [41] and Standards for Reporting Interventions in Clinical Trials of Acupuncture [42].

### Study design

This randomized, single-blind, sham-controlled neuroimaging study will be conducted at the affiliated hospital of Chengdu University of Traditional Chinese Medicine (CDUTCM), China. A total of 60 CID patients with GI disorder will be recruited using advertisements on posters and hospital networks. All patients meeting the inclusion criteria will randomly receive either 20 sessions of real acupuncture treatment or 20 sessions of sham acupuncture treatment. A multimodal MRI examination and evaluation will be performed at both baseline and the end of treatment. Additionally, 30 healthy controls (HCs) matched for age, sex, and education level will receive one multimodal MRI scan and a clinical assessment. A flowchart of the trial design is shown in Fig. 1, and the participant timeline is shown in Fig. 2.

**Fig. 1 Fig1:**
[figure not shown]
Flowchart of the trial. CID, chronic insomnia disorder; GI, gastrointestinal; MRI, magnetic resonance imaging

**Fig. 2 Fig2:**
[figure not shown]
Time schedule of enrolment, interventions and assessments. Eligible patients will be screened according to inclusion and exclusion criteria. These patients will then sign an informed consent form and undergo a medical examination. Eligible insomniacs will be randomly assigned to either the true or sham acupuncture groups and complete clinical and MRI assessments before treatment. After a 4-week treatment period, these patients will undergo clinical and MRI assessments again. In addition, adverse events will be recorded in the CRFs at any time during treatment. MRI, magnetic resonance imaging; PSQI, Pittsburgh sleep quality index; GSRS, gastrointestinal symptom rating scale; SAS, self-rating anxiety scale; SDS, self-rating depression scale

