#### Inclusion criteria

Patients diagnosed with CID are eligible to participate in the study. Inclusion criteria are (1) aged between 18 and 65 years, right-handed, any gender; (2) meets the CID diagnostic criteria in the International Classification of Sleep Disorders-Third Edition (ICSD-3) [43], and meets the criteria for spleen and stomach disharmony syndrome in the Clinical Terminology of Traditional Chinese Medical Diagnosis and Treatment—Syndromes (GB/T 16751.2-1997) [44]; (3) Pittsburgh Sleep Quality Index score above 7 (PSQI score > 7); (4) not taking any medication or health care products to improve sleep quality and experienced GI diseases at least 2 weeks before study enrollment; (5) has not participated in other clinical trials within the last month; and (6) agrees to voluntarily participate in the study and signs an informed consent form.

The HCs must meet the following inclusion criteria: (1) passes the neuropsychological tests and reports good sleep quality; (2) no GI symptoms; (3) all physiological indexes within the normal range following a physical examination, and no previous functional or organic disease or head injury; and (4) agrees to voluntarily participate in the study and signs an informed consent form.

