#### Exclusion criteria

Patients with any one of the following criteria will be excluded: (1) any severe conditions of the cardiovascular, cerebrovascular, liver, kidney, and hematopoietic systems; (2) secondary insomnia caused by drugs, cervical spondylosis, or other diseases; (3) history of psychiatric and neurological disorders or head trauma with loss of consciousness; (4) abuse of psychotropic drugs for anxiety and depression or sedative and hypnotic drugs; (5) pregnant, preparing for pregnancy, or lactating; and (6) any MRI contraindications such as claustrophobia, cardiac pacemaker, defibrillator, heart stenting, metal dentures, or intrauterine device.

The exclusion criteria for the HC are the same as for the patients.

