#### Withdrawal criteria

Participants with any of the following conditions will be withdrawn: (1) complications that affect safety, (2) serious adverse events, and (3) unwilling to follow the study protocol for examination and treatment.

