### Randomization and allocation concealment

A researcher ([name]), who will not be involved in the process of patient recruitment and treatment, will use SAS 9.2 software (SAS Institute Inc., Cary, NC, USA) to generate 60 random numbers and 60 serial numbers. Then, he will divide them into two groups based on random numbers and get the group numbers. These random numbers, serial numbers, and group numbers will be placed in opaque, sealed envelopes. Each sealed envelope will be numbered in sequence and kept in a safe place until the study is complete. If participants met the inclusion and exclusion criteria, envelopes with the same serial number will be opened in the order of enrollment by the same researcher ([name]) and the treatment allocation results will be forwarded to the acupuncturists. Except for the acupuncturists and the researchers who opened the envelopes, neither the participants nor the other researchers would know the participants' groups.

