### Blinding

The blinding of acupuncturists is quite difficult to achieve [51]. Patients will be told that they would be randomly assigned to one of two effective interventions after enrollment. During the treatment, patients will receive treatment in acupuncture treatment rooms with compartments to avoid relevant communication between patients. Acupuncturists will also be required to keep treatment plans secret. The names of the treatment and control groups will be replaced with meaningless letter combinations to prevent outcome assessors and statisticians from knowing how patients are grouped. Therefore, only patients, outcome assessors, and statisticians will be fully blind in this study.

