### Data analysis

#### Clinical data analysis

Statistical analyses of the clinical data will be performed using SPSS 20.0 statistical software (IBM Corporation, Armonk, NY, USA) and supervised by a skilled statistician blinded to group allocation. The Kolmogorov–Smirnov test will be used to test the normal distribution of continuous variables. Continuous normally distributed data will be reported as means and standard deviations; continuous non-normally distributed data will be expressed as medians with interquartile ranges. Categorical data will be presented as frequencies or percentages.

For the demographic and clinical information at baseline, the chi-squared test or Fisher’s exact test will be used for comparison of dichotomous data. The two-sample t test will be used for normally distributed continuous data or the Mann-Whitney U test for non-normally distributed data. To compare baseline and post-treatment changes in the same group, we will use the paired t test. Covariance analysis using baseline data as covariates will be used to compare the effects of different interventions on continuous data. In addition, gender differences and age differences may influence the data results. Therefore, in order to avoid the influence of gender, age and other factors on the data, we will also adopt covariance analysis, taking gender, age, and other factors as covariates respectively, and conduct covariance analysis with continuous data. A p value < 0.05 will be considered statistically significant.

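### Allocation appears to come before the baseline assessments, so a refused or unusable baseline scan becomes an avoidable post-randomisation loss

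*Protocol article*

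**What the plan says.** The Fig. 2 legend of the protocol article goes through the trial in order: screening, consent and medical examination, then "Eligible insomniacs will be randomly assigned to either the true or sham acupuncture groups and complete clinical and MRI assessments before treatment", then four weeks of treatment and reassessment.

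The section on randomisation and allocation concealment gives the trigger for allocation: "If participants met the inclusion and exclusion criteria, envelopes with the same serial number will be opened in the order of enrollment". The result then goes to the acupuncturists. The list holds 60 random numbers and 60 serial numbers, and the article describes no spare allocations.

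Other parts of the article that bear on the point:

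- **Inclusion criteria:** "Pittsburgh Sleep Quality Index score above 7 (PSQI score > 7", so a PSQI score is needed to establish eligibility.
- **Exclusion criteria:** "any MRI contraindications such as claustrophobia, cardiac pacemaker, defibrillator, heart stenting, metal dentures, or intrauterine device".
- **Withdrawal criteria:** these cover a participant who is "unwilling to follow the study protocol for examination and treatment".
- **Primary outcomes:** this section names MRI indicators alongside PSQI (the abstract names PSQI alone).
- **Clinical data analysis:** "Covariance analysis using baseline data as covariates will be used to compare the effects of different interventions on continuous data".
- **Blinding:** "Therefore, only patients, outcome assessors, and statisticians will be fully blind in this study".

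**The concern.** Baseline assessments are best finished before the arm is assigned. A patient who cannot or will not complete them is then a screening failure and costs the trial nothing. If the envelope is opened first, the same patient is already randomised.

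This matters here because the baseline MRI is both demanding and essential. Without a usable first scan there is no MRI change measure, and MRI indicators are among the outcomes called primary. The sample size section itself expects head movement to spoil some scans. Screening for contraindications removes foreseeable problems such as claustrophobia, but it does not detect motion, poor image quality or a later refusal. Each such case uses up one of 60 allocations and leaves the MRI comparison with fewer patients than were randomised. If the patient is also withdrawn for declining the examination, the PSQI may be lost as well.

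**Working it through.** **1. Order of events**

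| Source | What it fixes | What it leaves open |
|---|---|---|
| Fig. 2 legend | Assignment is named first, then clinical and MRI assessments; both precede treatment | The two are joined only by *and*; the figure is not shown |
| Randomisation section | The envelope is opened when eligibility criteria are met | Whether baseline is already complete |
| Study design; Outcome measures | Assessments at baseline and after treatment | Position of baseline relative to allocation |
| Inclusion criteria | A PSQI exists before allocation | Whether that score is the baseline covariate |

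No section makes a completed baseline a condition for opening the envelope. The two passages that speak to timing point the same way, so allocation first is the natural reading, though not a certain one.

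**2. The plan's own sample size**

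Inputs from the Sample size section: difference 4.5 − 1.8 = 2.7, SD 3, α 0.05 (taken as two-sided), power 0.9.

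- Normal approximation: n = 2 × (1.960 + 1.282)² × (3/2.7)² ≈ 25.9, so 26 per arm.
- Two-sample t-test with standardised difference 2.7/3 = 0.9: n = 26.94, so 27 per arm.

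The stated 27 is therefore reproduced as a per-arm figure.

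**3. What the increase to 30 covers**

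27/(1 − 0.10) = 30, so the allowance absorbs a 10% loss from all causes. At 15% loss, 27/0.85 = 31.8, so 32 per arm would be needed.

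Two-sided t-test power for PSQI if patients are lost equally from both arms and **their PSQI is lost too**:

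| Remaining per arm | Loss from 30 | Power |
|---|---|---|
| 30 | 0% | 92.9% |
| 27 | 10% | 90.1% |
| 24 | 20% | 86.3% |
| 20 | 33% | 79.2% |

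**4. Possible size of the baseline-scan loss**

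The documents give no rate of refused or unusable baseline scans. Assuming 5–10%: 0.05 × 60 = 3 and 0.10 × 60 = 6 patients. The PSQI allowance is 60 − 2 × 27 = 6 patients. At the upper end, and only if every one of these patients also lost the PSQI, the whole allowance would be gone before treatment starts, with power still at about the planned 90%. Dropout over 20 sessions would then come on top.

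**5. The imaging margin**

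The 27 belongs to PSQI. For imaging, the same section cites 12–26 per group, so the margin from 30 is 30 − 26 = 4 to 30 − 12 = 18 per arm. That margin must also cover unusable second scans and the MRI data that the imaging analysis section excludes for patients who took drugs.

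**The case against.** The strongest reply is that the order is not established. One legend sentence joins two actions with *and*, its only explicit time limit is the start of treatment, and the figures that might settle it are not shown. This stands as a caution. It does not remove the point, because the randomisation section independently ties the envelope to eligibility alone.

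A reader might infer that all baseline values, including the PSQI covariate, are open to influence from the allocation. The documents do not support that. A PSQI exists before allocation for every patient, though the article does not say whether it serves as the covariate. Only the envelope opener and the acupuncturists know the arm. Patients and outcome assessors are blind, PSQI, SAS and SDS are self-rated, and no treatment has been given. No clear route to material bias remains. For the same reason, failure of the baseline scan should not depend on arm, so any imbalance between arms would be due to chance.

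A reader might also infer that failed scans consume the margin of three patients per arm. That margin comes from the PSQI calculation. A patient whose scan is spoiled by motion still has a PSQI, and nothing in the article removes it. Only a refusal that leads to withdrawal would plausibly cost both, and the withdrawal criteria do not say that PSQI data already collected are discarded.

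Finally, the remedy has drawbacks. Scanning takes place at a different institution, so an image check before allocation needs some organisation. Requiring a usable scan also limits the PSQI comparison to patients who can be scanned, although the first aim is clinical efficacy. And nothing shown forbids repeating a failed scan before treatment under the present order. These are fair costs, but a refusal or a repeated failure would still fall after randomisation.

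**Conclusion.** The point holds as a cheap and worthwhile improvement; it is not a serious flaw. On the natural reading, patients are allocated at eligibility and complete the baseline scales and MRI afterwards. A refused or unusable first scan is then an avoidable post-randomisation loss for the MRI primary outcomes and uses one of 60 allocations. It reaches PSQI only if the patient is withdrawn and the score is lost.

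The size cannot be taken from the documents. Under an assumed 5–10% it is 3–6 patients in all. For PSQI, planned power of 90% is kept as long as losses from all causes stay within about 10%. Bias in the baseline covariates is a secondary and probably small matter. The conclusion rests on reading the Fig. 2 legend together with the randomisation section; if the sponsor already completes baseline first, one clarifying sentence settles it.

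**What to change.** Amend the Fig. 2 legend (and the figure if needed) and the section on randomisation and allocation concealment. The envelope should be opened only after the baseline PSQI, GSRS, SAS and SDS are complete and the baseline MRI has been checked as usable. A failed scan is repeated, or the patient is counted as a screening failure, before an envelope is used.

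The steps are already planned and only change order. The costs are a short delay between eligibility and allocation, a prompt image check, and a PSQI comparison restricted to patients with a usable scan, which the report should state.

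For patients already randomised before baseline, keep all of them in the PSQI analysis whatever their MRI status, and report pre-treatment losses by arm.

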#### Recruitment

Study participants will be recruited mainly from outpatient clinics in major hospitals in Chengdu. We will post the recruitment advertisements approved by the ETHICS committee on the poster boards of each hospital and promote them through WeChat software (Tencent Inc., Shenzhen, China). The entire recruitment process will be conducted by researchers ([name] and [name]) who are not involved in the treatment process.

